## 3. Discussion

Patients with sABI are characterized by high clinical complexity, severe cognitive motor disabilities, and an increased risk of developing clinical complications [42,43,44]. An appropriate and skilled comprehensive rehabilitation intervention can significantly impact clinical outcomes and improve the quality of life of patients and their caregivers [1,2,45,46,47]. An early verticalization can promote patients’ recovery and prevent cognitive-motor disabilities and clinical sequelae [3,4,5]. The present multicenter VEM-sABI study will provide new insights into the still-debated efficacy and usability of a device considered safer for verticalization of patients with sABI because it combines robotic verticalization with lower limb mobilization [12]. The study aims to achieve several outcomes. Firstly, it is expected to enroll a large and homogeneous cohort of patients with sABI admitted to post-acute rehabilitation settings. This goal could minimize the methodological bias of the available literature on this field, which most often involved small and heterogeneous patient cohorts (e.g., chronic patients with sequelae of sABI) [5,8,12,13,14]. In addition, we planned to specifically address this topic in post-acute rehabilitation, where the likelihood of patient clinical improvements due to neuroplasticity [18] and the occurrence of clinical complications are higher [42,43,44]. Moreover, we expect that the two cohorts of patients allocated in the experimental and control arm will not differ in terms of demographic and anamnestic characteristics, to avoid biases in evaluating efficacy and usability of the two treatments. Conversely, differences in clinical characteristics and cognitive functions between patients with pDoC and those eDoC are expected. For this reason, targeted clinical and neurophysiological measures will be adopted to detect specific changes in outcome as a function of clinical diagnosis and to identify patients’ profiles with high probability to respond to both (or at least one of the two) treatments. Additionally, we expect the following study outcomes from the data analysis: (i) an improvement of cognitive levels, disability, and motor function at the end of the treatment in both arms, with a significant recovery in the VEM group, in accordance with previous studies [14]; (ii) a more consistent improvement of lower limb strength, and higher reduction in spasticity in the VEM group because of combined controlled mobilization in the VEM device; (iii) lower occurrence of side effects (e.g., orthostatic hypotension) and related dropouts in the VEM arm; (iv) higher occurrence of discontinuation of verticalization due to “treatment futility” in the eDoC patients, as they are more susceptible to early regain vertical posture and gait. A further analysis of motivations of dropouts will identify clinical profiles of patients who could better match the robotic (VEM) or the traditional tilt table treatment (TV); (v) a reduction in clinical complications occurrence in both groups, based on the potential impact of verticalization on patients overall clinical stabilization [3,4]. Because most participating centers are not familiar with this robotic technology in rehabilitation of patients with sABI, we expect to see higher therapist’s compliance for traditional tilt table (i.e., higher SUS score), especially in the early stages of the study. A preliminary structured 3-day training provided by the robotic device manufacturer, on the appropriate use of the robotic device, including real-life testing on at least two different patients, will be performed to avoid potential challenges and ensure the homogeneity in the device use. To ensure ongoing protocol fidelity and inter-site consistency, we implemented the following measures: (i) competency checklist for certification to assess each operator’s ability to manage setup, tilt procedures, stepping control, safety monitoring, and patient interaction; (ii) monitoring parameters (stepping frequency, tilt parameters, adverse events). Ongoing technical and clinical support, throughout constant availability via phone calls and monthly video-call meetings, will be further provided by the coordinator to address possible concerns. We also forecast to identify changes in neurophysiological indices (as measured by EEG) and blood-biomarkers of brain plasticity in patients who will present clinical improvements. In addition, we hope that neurophysiology and biomarkers can detect any sub-clinical (para-clinical) changes caused by the two verticalization procedures. Thus, the two outcome measures will be able to provide useful information to identify patients with a high probability of response to verticalization and help clinicians plan the most appropriate and personalized treatment in such a specific population of patients with sABI.

This trial has several potential limitations. Firstly, the mandatory timing of the study, due to the expected expiration of the funded project, will not allow the long-term effect of the treatment to be investigated. At the end of data collection, if deemed feasible, we hope to be able to follow up some patients over the long term after requesting an amendment from the ethics committee. In general, further studies on large cohorts of patients will be needed to assess patients’ progress after discharge from post-acute rehabilitation.

Secondly, patients will receive the usual care in addition to the experimental or control intervention. Given the different centers participating in the trial, this might act as a confounding factor. However, only Italian centers participated in the trial: in Italy, post-acute rehabilitation is regulated by national legislation, and only minor differences may vary from region to region. For example, the time that is dedicated to the daily rehabilitation of each patient is homogeneous across centers. In addition, any critical differences in usual care between the different centers were discussed and ironed out during initial protocol sharing meetings.

Thirdly, here we only focused on the effect of robotic verticalization vs. traditional verticalization on patients’ outcomes, overlooking possible effects on family caregivers’ satisfaction and burden. Due to limited resources, we could not assess this matter here, but we hope to investigate it in future studies.

Fourthly, for the exploratory analysis of serum biomarkers, serum samples will be initially stored at −20 °C due to the unavailability of −80 °C storage facilities at the participating clinical sites. Storage at −80 °C is generally recommended for the long-term preservation of biomarkers such as NF-L and GFAP, but recent evidence supports the long-term stability of these proteins at −20 °C. In particular, a study by Di Muro et al. [48], conducted on bovine samples, demonstrated that NF-L concentrations in both cerebrospinal fluid and serum remained stable at −20 °C and −80 °C over a median storage period of 16.5 months (IQR: 9–20 months). Notably, concentrations were measured using the same automated ELISA platform planned for use in our study, ensuring methodological consistency. Although potential degradation cannot be completely ruled out, these findings support the reliability of our short-term storage approach.

Notwithstanding this limitation, the VEM-sABI trial will provide new insights into the efficacy, safety, and usability of robot-assisted rehabilitation and offer clinicians useful information to take advantage of technological advances to plan an appropriate and tailored rehabilitation in the post-acute phase of such a complex population.

## Figures and Tables

**Figure 1 jcm-14-06628-f001:**
[figure not shown]
CONSORT flow diagram. Abbreviations: sABI = severe Acquired Brain Injury; TV = Traditional Verticalization; VEM = robotic Verticalization and Mobilization.

**Table 1 jcm-14-06628-t001:** Schedule of enrolment, interventions, and assessments from the VEM-sABI study. Each week includes 5 intervention sessions of 30 min duration provided on a daily basis.

Time Point/ Measure	Pre-Randomization	Randomization	Post-Randomization						
	Enrolment	T0 (At the Start of Intervention)	Week 1	Week 2	Week 3	Week 4	Week 5	T1 (After the End of the Intervention)	T2 (1 Month After T1)
Informed consent	X								
Eligibility screening	X								
Allocation		X							
Clinical and anamnestic data collection		X							
Interventions:									
VEM			X	X	X	X	X		
TV			X	X	X	X	X		
Outcomes:									
LCF		X						X	X
CRS-R		X						X	X
mBI		X						X	X
DRS		X						X	X
SUS								X	
MAS		X						X	X
MRC		X						X	X
FDG-CCS		X						X	X
ABS			X	X	X	X	X		
NCS-R			X	X	X	X	X		
30 min standard EEG		X						X	X
Blood sampling		X							X
AER			X	X	X	X	X	X	X

X indicate that activities (rows) are performed at specific time points (columns). Abbreviations: ABS = Agitated Behavior Scale; AER = Adverse Events Report; CRS-R = Coma Recovery Scale-Revised; DRS = Disability Rating Scale; EEG = Electroencephalogram; FDG-CCS = Fondazione Don Gnocchi-Clinical Complication Scale; LCF = Levels of Cognitive Functioning; MAS = Modified Ashworth Scale; MRC = Medical Research Council scale; mBI = modified Barthel Index; NCS-R = Nociception Coma Scale-Revised; SUS = System Usability Scale; TV = Traditional Verticalization; VEM = robotic VErticalization and Mobilization.

**Table 2 jcm-14-06628-t002:** Inclusion and exclusion criteria.

Inclusion Criteria	Exclusion Criteria
Age between 18 and 75 years; sABI due to traumatic, vascular, anoxic, or mixed etiology; Stable behavioral/cognitive diagnosis on at least 4 behavioral evaluations in 1 week using the Italian version of the CRS-R in patients with pDoC, or the LCF-based cognitive assessment in patients with eDoC; Time post-injury between 28 days and 6 months [1]; Not recovered upright station; Written informed consent by the patient’s legal representative/primary caregiver.	Severe medical conditions hampering verticalization (e.g., severe hypotension or conditions realizing hemodynamic instability, end stage or severe symptomatic heart failure with reduced ejection fraction, cardiac arrhythmia of new diagnosis or arrhythmic flare, severe hepatic failure, chronic severe lower limb arterio-venous disease, sepsis/septic shock, thrombus venous embolism of new diagnosis, severe autonomic dysreflexia); Severe medical conditions hampering lower limb mobilization (e.g., fractures, heterotopic ossifications); Severe medical conditions impacting EEG activity (e.g., sub-continuous or abundant EEG epileptiform abnormalities); Severe medical conditions influencing consciousness/cognitive status, such as severe hyponatremia or hypoglycemia; Contraindications to the use of Erigo^®^Basic and/or Erigo^®^Pro (Hocoma, Volketswil, Switzerland) as per technical data sheet (see Appendix A); Presence of prohibited drugs (see Appendix B).

Abbreviations: CRS-R = Coma Recovery Scale-Revised; eDoC = emergence from Disorder of Consciousness; EEG = electroencephalography; LCF = Level of Cognitive Functioning; pDoC = prolonged Disorder of Consciousness; sABI = severe Acquired Brain Injury.

**Table 3 jcm-14-06628-t003:** Summary of primary, secondary, and exploratory outcomes and measures.

Outcome	Timing, Measure
Primary outcome: Global cognitive functioning	At T0 and T1: LCF
Secondary outcomes:	
Functional disability Spasticity of lower limbs Muscular strength of lower limbs Functional independence Usability of devices from physiotherapists Adverse events	At T0, T1 and T2: DRS At T0, T1 and at T2: MAS At T0, T1 and T2: MRC. Additional clinical observation of spontaneous or reflex movement to pain stimulation in pDoC patients At T0, T1 and T2: mBI At T1: SUS Each daily session: AER
Exploratory outcomes:	
Level of consciousness in pDoC Burden of clinical complications Neurophysiological indices of brain functionality Blood biomarkers of brain plasticity Changes in cognitive functioning at 1 month after treatment Pain Overall compliance	At T0, T1 and T2: CRS-R At T0, T1 and T2: FDG-CCS At T0, T1 and T2: qualitative (background activity, reactivity) and quantitative (power spectrum, microstates, connectivity) EEG measures At T0 and T2: Serum level of BDNF, NF-L, GFAP At T0 and T2: LCF Each daily session: VAS (for eDoC patients) or NCS-R (for pDoC) Each daily session: ABS

Abbreviations: ABS = Agitated Behavior Scale; AER = Adverse Events Report; BDNF = Brain-Derived Neurotrophic Factor; CRS-R = Coma Recovery Scale Revised; DRS = Disability Rating Scale; eDoC = emerged from DoC; EEG = Electroencephalogram; FDG-CCS = Fondazione Don Gnocchi Clinical Complication Scale; GFAP = Glial Fibrillary Acid Protein; LCF = Levels of Cognitive Functioning; MAS = Modified Ashworth Scale; mBI = modified Barthel Index; MRC = Medical Research Council; NCS-R = Nociception Coma Scale-Revised; NF-L = Neurofilament Light chain; pDoC= prolonged Disorder of Consciousness; SUS = System Usability Scale; VAS = Visual Analogue Scale.

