## 1. Introduction

Survivors from a severe Acquired Brain Injury (sABI; i.e., severe traumatic or non-traumatic brain injury leading to a comatose state with a Glasgow Coma Scale ≤ 8 for at least 24 h in the acute phase) can persist in a clinical condition of prolonged Disorder of Consciousness (pDoC; i.e., patients in vegetative state/unresponsive wakefulness syndrome, VS/UWS, or in minimally conscious state, MCS) or emerge from DoC (eDoC) with a moderate or severe cognitive motor disability [1]. Both American and Italian guidelines recommended an early post-acute admission of such complex disabled individuals in specialized rehabilitation units with high expertise in multidisciplinary care and multimodal diagnosis and prognosis [1,2]. These dedicated settings provide a comprehensive rehabilitation program that includes medical stabilization, alternate positioning, motor and cognitive training and speech therapy, to prevent and treat clinical complications (e.g., contractures, spasticity, and heterotopic ossifications) and to facilitate recovery of cognitive-motor and functional abilities.

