#### 2.3.2. Trial Protocol

After screening for inclusion/exclusion criteria, a patient is enrolled in the trial and the following demographic and anamnestic variables will be collected: age, sex, education; medical history: time post-injury (TPI), etiology, morphometry and location of brain injury by brain CT scan; pharmacological therapy affecting arousal (e.g., neurosedatives); clinical diagnosis of pDoC (i.e., VS/UWS or MCS) or of eDoC according to standardized clinical criteria [1].

Within one week from enrolment (T0), the enrolled patients will undergo clinical-functional evaluations, neurophysiological assessments and serum blood sampling at study entry as described in Table 3 for primary, secondary, and exploratory outcomes. After the entry evaluation (T0), patients will perform a total of 25 (5 per week for 5 consecutive weeks) 30 min VEM or TV sessions in the same period of the day. Both interventions (i.e., VEM and TV) are non-invasive, utilize CE-marked medical devices, and are routinely used in neurorehabilitation practice. The devices comply with the EU Medical Device Regulation (MDR 2017/745).

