In each daily session, patients will be gradually verticalized (from supine up to a maximum of 90° upright position), using a combined robotic-assisted tilt table with lower limb mobilization, Erigo^®^ (Hocoma, Volketswil, Switzerland), (VEM group) or conventional non-robotic tilt table (TV group). The robotic device combines verticalization with rhythmic controlled passive alternating loading and unloading of the legs of which protocol (e.g., simple stepping, sinus walking) will be set up depending on the patient’s osteoarticular condition (e.g., range of movement = 45°; pace = 24 steps/min), without functional electric stimulation. Legs stepping movements will be obtained with the rhythmic alternating feet pushing up that will be tailored from complete (100% of assistance) to no (0% of assistance) passive mobilization for each limb according to the patient’s motor and cognitive ability and side effects such as pain (see Appendix A for the list of available tasks). Similarly, patients assigned to the TV group will be gradually verticalized (from supine up to a maximum of 90° upright position), according to the patient’s clinical, motor, and cognitive status, using a traditional tilt table. The verticalization in both arms of the trial, and the stepping frequency, and the percentage of assistance for each leg in VEM, will be tailored based on patients’ vital parameters, tolerance to verticalization, and pain (see outcome measures below). VEM and TV training will be performed with the supervision of a physiotherapist and a physician will be always available in case of emergency. In the robotic arm, blood pressure drops were managed—before tilt reversal—by increasing stepping frequency or encouraging active pedaling in conscious patients. These strategies were not available in the traditional tilt-table group, where blood pressure (BP) recovery relied solely on repositioning.

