### 2.4. Outcome Measures

Almost all measures will be collected at study entry (T0) and at T1 and T2 to evaluate the (possible) changes in the two follow-ups with respect to T0. Primary, secondary, and exploratory outcomes and related measures are summarized in Table 3.

The clinical–functional evaluation includes the following:-The Level of Cognitive Functioning (LCF) [24,25], an observer-rated scale (from coma to purposeful appropriate behavior) divided into eight levels that describe the patterns or stages of recovery typically seen after a brain injury.-The Coma Recovery Scale-Revised (CRS-R) [23,26] is an observer-rated tool designed to assess patients with disorders of consciousness. It evaluates auditory, visual, motor, oromotor/verbal, communication, and arousal functions to help differentiate between vegetative state, minimally conscious state, and emergence from these conditions.-The Disability Rating Scale (DRS) [27], an observer-rated, 30-point continuous scale that provides quantitative information to document the progress of patients with severe brain injury from coma to community reintegration. It evaluates 8 areas of functioning, organized into 4 categories: (1) consciousness (eye opening, verbal response, motor response); (2) cognitive ability (feeding, toileting, grooming); (3) dependence on others; (4) employability. Each area of functioning is rated on a scale of 0 to either 3, 4, or 5 (maximum score = 30-death, minimum score = 0-person without disability) with the highest scores representing the higher level of disability.-The Modified Ashworth Scale (MAS) [28], an observer-rated scale used to measure muscle spasticity by assessing resistance during passive soft-tissue stretching. Scores range from 0 (no increase in muscle tone) to 4 (rigid in flexion or extension).-The Medical Research Council (MRC) scale [29], an observer-rated scale for assessing muscle strength, scoring from 0 (no contraction) to 5 (normal strength) in specific muscle groups.-The Fondazione Don Gnocchi Clinical Complication Scale (FDG-CCS) [30], an observer-rated tool for recording and grading clinical complications during rehabilitation of patients with sABI, covering medical, nursing, and functional events to support patient monitoring and care planning.-The modified Barthel Index (mBI) [31], an observer-rated continuous scale for evaluation of ability to perform autonomously personal activities of daily living. It measures physical disability across 10 categories that are scored from 0 to either 5, 10, or 15 (maximum score = 100-independence, minimum score = 0-complete dependence) with the highest scores representing the higher level of independence.-The System Usability Scale (SUS) [32] is a simple, ten-item 5-point Likert scale giving a global view of subjective assessments of usability, including effectiveness, efficiency, and satisfaction of a device. Higher scores correspond to higher usability.-The Nociception Coma Scale–Revised (NCS-R) [33], an observer-rated tool to assess pain-related behaviors in patients with disorders of consciousness. It evaluates motor, verbal, and facial responses to noxious stimulation, with higher scores indicating stronger nociceptive responses. -The Agitated Behaviour Scale (ABS) [34], an observer-rated scale measuring the nature and extent of agitation during recovery from brain injury. It assesses behavioral, emotional, and cognitive components, with higher scores indicating greater agitation severity.

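### Table 3 measures the exploratory outcome 'Overall compliance' only with the Agitated Behaviour Scale, which rates agitation and carries no information on sessions attended, their duration or the tilt reached

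*Protocol article*

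**What the plan says.** Table 3 of the protocol article lists the exploratory outcomes in one column and the timing and measure in the other. The outcome column closes with "Changes in cognitive functioning at 1 month after treatment Pain Overall compliance", and the measure column closes with "or NCS-R (for pDoC) Each daily session: ABS".

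Section 2.4 (Outcome Measures) describes the ABS as "an observer-rated scale measuring the nature and extent of agitation during recovery from brain injury", "with higher scores indicating greater agitation severity". It gives no rule for turning an ABS score into a statement about compliance, and the article does not define overall compliance.

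On the planned amount of treatment, Section 2.3.2 says that "patients will perform a total of 25 (5 per week for 5 consecutive weeks) 30 min VEM or TV sessions". In both arms verticalization "will be tailored based on patients’ vital parameters, tolerance to verticalization, and pain", so the amount delivered may differ from patient to patient. The Discussion lists "monitoring parameters (stepping frequency, tilt parameters, adverse events" among the measures for keeping the intervention consistent across sites.

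**The concern.** The outcome's name and its instrument do not match. A reader who sees a compliance result will expect to learn whether patients received or went along with the treatment. The ABS answers a different question: how agitated they were.

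The mismatch matters more in this population than in most. The Introduction includes "patients in vegetative state/unresponsive wakefulness syndrome, VS/UWS, or in minimally conscious state, MCS". Such a patient may show little agitation because he or she shows little behaviour of any kind. A recovering, restless patient may score high while completing every session. Reported as compliance, the score would partly reflect level of consciousness.

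**Working it through.** No formula applies and the plan states no figure for this outcome. The check sets the relevant parts of the article side by side.

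1. **Pairing in Table 3.** In the text at hand the table's columns run on as lists, so I matched the entries by order:
   - level of consciousness: CRS-R
   - clinical complications: FDG-CCS
   - neurophysiology: EEG
   - blood biomarkers: serum BDNF, NF-L and GFAP
   - cognition at one month: LCF
   - pain: VAS or NCS-R
   - overall compliance: ABS at each daily session

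   Seven outcomes meet seven measures and none is left over. The first six pairs are plainly right, which supports the seventh.

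2. **What the ABS holds.** By Section 2.4 it holds behavioural, emotional and cognitive components of agitation. It has no entry for attendance, minutes or tilt. It is rated at each daily session, so I infer that a missed session yields no rating.

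3. **Two readings of compliance.**
   - *Delivery of treatment.* The ABS does not measure it, by step 2.
   - *Behavioural cooperation.* The ABS is closer to this, but a low score does not separate a cooperative patient from an unresponsive one. The neighbouring pain row uses different tools for eDoC (VAS) and pDoC (NCS-R). The compliance row uses one scale for everyone.

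4. **Other uses of the same terms.** Section 2.3.2 gives agitation as an example of the adverse event for excessive pain or discomfort. The Discussion uses compliance for therapists and equates it with a higher SUS score. So agitation is read under two headings, and compliance has two unrelated measures.

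5. **Where delivery is tracked.** Section 2.6 makes missing two consecutive sessions, or more than five in total, a protocol violation, so missed sessions have to be counted. Section 2.3.2 grades an event that interrupts a single session as a moderate adverse event. The Discussion names tilt parameters for monitoring. None of these is tied to the compliance outcome in Table 3.

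6. **Scale of the quantity the ABS cannot show.** Planned: 25 × 30 min = 750 min. With five sessions missed: 20 × 30 min = 600 min. The difference is 150/750 = 20%. This range only restates the attendance rule. It is not an error that the ABS produces in any estimate, and patients who violate the rule still enter the intention-to-treat analysis of Section 2.6, so it is not the dose range of the analysed population either.

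**The case against.** The strongest reply is that the article never calls this outcome adherence. Compliance does not appear among the aims in the Introduction or in the statistical plan of Section 2.6. If the authors mean behavioural tolerance of the session, a per-session agitation rating is a reasonable choice and the defect is loose wording. This stands in part: on that reading, renaming the row removes most of the problem. What remains is that the article does not say so, and that low agitation is hard to read as cooperation in an unresponsive patient.

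The second reply is that delivery is not lost. A session cut short for hypotension reaches the Adverse Events Report, and adverse events are a secondary outcome. Missed sessions must be counted and tilt parameters are monitored. This also stands, and it limits the consequence. It does not change what Table 3 names as the measure of compliance. The monitoring is described alongside training on the robotic device, and recording of tilt in the TV arm is not spelled out. A condensed article may leave such record-keeping to the full protocol, so I make no finding of that.

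A reader might infer three stronger points, and the article supports none of them:
- *That a comparison of adherence between arms is invalid.* No such comparison is specified.
- *That an unresponsive patient is scored as fully compliant.* No scoring rule or threshold for compliance exists. Only the direction of the ABS score is given.
- *That the trial cannot tell under-delivery from inefficacy, or stepping from time upright.* Much of delivery could be rebuilt from the records above. Separating stepping from time upright is not a stated aim, since VEM and TV are compared as tailored packages.

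**Conclusion.** The point holds as a mismatch between a stated outcome and its stated measure. Followed as written, Table 3 would have the trial report overall compliance from an agitation score that carries nothing about attendance, duration or tilt, and that can be low simply because the patient is unresponsive. Such a result would be misleading.

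The severity is minor. This is the last of seven exploratory outcomes, and no power or sample-size figure depends on it. The primary LCF analysis and the error rate are unaffected, and safety reporting does not rely on it. The conclusion rests on two assumptions: that the table rows pair in order, and that the ABS is used as Section 2.4 describes it, with no undisclosed conversion to compliance.

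**What to change.** In Table 3, relabel the ABS row as agitation during sessions and keep the scale and its timing. Then define overall compliance from delivery records:

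- sessions completed out of 25, from the counts already needed for the missed-session rule in Section 2.6;
- sessions interrupted early, from the moderate adverse event grading in Section 2.3.2, extended to interruptions for other reasons;
- minutes completed and maximum tilt reached, where recorded.

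Capture these the same way in VEM and TV and summarise them by arm. If only behavioural cooperation was meant, the relabelling alone removes the mismatch, and the compliance outcome can be dropped or defined separately.

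The cost is a change to one part of Table 3 and minor extra data entry in the TV arm. The change is best made early, because minutes and tilt that were not noted at the session may not be recoverable later.
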